## Abstract

**Background:**

Early recognition and treatment of sepsis is crucial to prevent detrimental outcomes. General practitioners (GPs) are often the first healthcare providers to encounter seriously ill patients. The aim of this study is to assess the value of clinical information and additional tests to develop a clinical prediction rule to support early diagnosis and management of sepsis by GPs.

**Methods:**

We will perform a diagnostic study in the setting of out-of-hours home visits in four GP cooperatives in the Netherlands. Acutely ill adult patients suspected of a serious infection will be screened for eligibility by the GP. The following candidate predictors will be prospectively recorded: (1) age, (2) body temperature, (3) systolic blood pressure, (4) heart rate, (5) respiratory rate, (6) peripheral oxygen saturation, (7) mental status, (8) history of rigors, and (9) rate of progression. After clinical assessment by the GP, blood samples will be collected in all patients to measure C-reactive protein, lactate, and procalcitonin. All patients will receive care as usual. The primary outcome is the presence or absence of sepsis within 72 h after inclusion, according to an expert panel. The need for hospital treatment for any indication will be assessed by the expert panel as a secondary outcome. Multivariable logistic regression will be used to design an optimal prediction model first and subsequently derive a simplified clinical prediction rule that enhances feasibility of using the model in daily clinical practice. Bootstrapping will be performed for internal validation of both the optimal model and simplified prediction rule. Performance of both models will be compared to existing clinical prediction rules for sepsis.

**Discussion:**

This study will enable us to develop a clinical prediction rule for the recognition of sepsis in a high-risk primary care setting to aid in the decision which patients have to be immediately referred to a hospital and who can be safely treated at home. As clinical signs and blood samples will be obtained prospectively, near-complete data will be available for analyses. External validation will be needed before implementation in routine care and to determine in which pre-hospital settings care can be improved using the prediction rule.

**Trial registration:**

The study is registered in the Netherlands Trial Registry (registration number NTR7026).

## Background

Sepsis is a life-threatening complication of an infection. Early detection and initiation of adequate treatment is the key factor influencing outcome [1–4]. It is estimated that annually, 49 million people suffer from sepsis worldwide, of which 11 million do not survive [5]. In 2017, the WHO declared sepsis a global healthcare priority and urged member states to improve recognition and treatment of sepsis [6]. Global efforts to reduce mortality and morbidity from sepsis have focused on hospital settings, but patients often present in primary care in the early stages of sepsis. General practitioners (GPs) are confronted with acutely ill patients with a variety of symptoms, signs, and potential diagnoses. Within minutes, they have to decide whether a patient can safely be treated at home or should be referred to a hospital for further assessment.

In the Netherlands, out-of-hours primary care is provided by large GP cooperatives [7]. Patients are only assessed by a GP if the medical complaint cannot wait until the following working day. In contrast to other common time-critical conditions such as stroke and myocardial infarction, patients with sepsis are more likely to contact a GP cooperative instead of an emergency medical service prior to hospital treatment [8]. Data from our preliminary research on patients admitted to an intensive care unit (ICU) due to community-acquired sepsis showed that about half of the patients had prior contact with a GP cooperative. Two thirds of these patients were referred to the hospital after the first contact [9]. The majority of the patients were assessed during a home visit.

## Methods

### Setting and design

We will perform a prospective diagnostic cohort study in the Netherlands in four GP cooperatives (Ede,’s-Hertogenbosch, Uden, and Oss) for out-of-hours primary care. The cooperatives serve a total of approximately 830,000 inhabitants in a mixed urban, suburban, and rural area. The cooperatives are based in or adjacent to regional hospitals.

### Patients

Patients will be recruited during out-of-hours home visits by GPs. Patients only receive home visits when they have acute medical complaints that cannot wait until the next working day and they are not able to visit the GP cooperative location for a clinic consultation. This is decided after telephone assessment by a triage nurse based on the Netherlands Triage System (NTS) [16].

#### Inclusion criteria

Acutely ill adult patients (≥ 18 years), receiving a home visit by a GP during OOHFever, confusion, or general deterioration or otherwise suspected of a serious infection

#### Exclusion criteria

Non-infectious cause of the acute complaints (e.g. stroke or myocardial infarction)Hospitalisation within 7 days before the home visitCondition that requires secondary care assessment if there are any signs of systemic infection (e.g. chemotherapy with possible neutropenia)Terminal illness or other reason not to refer the patient to a hospital despite presence of a life-threatening condition.

### Candidate predictors

We selected nine clinical features and three blood tests as candidate predictors for the development of the clinical prediction model (Table 1). Parameters of widely used scoring systems such as the SIRS, qSOFA, and National Early Warning Score (NEWS) [18] were considered, as well as clinical features used in guidelines such as the Netherlands Triage Standard (NTS) and NICE Sepsis guideline [17]. Candidate predictors were selected if there was evidence to suggest that they might usefully contribute to the diagnosis of sepsis and if they can be easily and objectively measured by GPs.

**Table 1 Tab1:** Candidate predictors eligible for the selection in the prediction model

Type of predictor	Candidate predictor	Measurement method	Measurement unit	Used in
Clinical feature	Age	Inclusion date minus date of birth	Years	NICE guideline [17]
	Body temperature	Tympanic measurement	°C	SIRS [10], NEWS [18], NICE guideline
	Heart rate	IntelliVue MP2/X2	Beats/min	SIRS, NEWS, NICE guideline
	Respiratory rate	IntelliVue MP2/X2 or GP assessment	Breaths/min	SIRS, qSOFA, NICE guideline, NEWS
	Systolic blood pressure	IntelliVue MP2/X2	mmHg	qSOFA, NEWS, NICE guideline
	Peripheral oxygen saturation	IntelliVue MP2/X2	%	NEWS, NICE guideline
	Mental status	GP assessment	Normal/altered	qSOFA, NEWS, NICE guideline
	Rapid progression of illness in last 24 h	GP assessment	Yes/no	NICE guideline
	(History of) rigors in last 24 h	GP assessment	Yes/no	NTS [16]
Blood test	C-reactive protein (CRP)	Siemens, ADVIA Chemistry XPT	mg/l	
	Lactate	StatStrip Xpress	mmol/l	
	Procalcitonin (PCT)	Siemens, ADVIA Centaur XPT	ng/ml	

Candidate blood tests had to be currently used in the hospital setting for the diagnosis and/or prognosis of sepsis, and, preferably, to be available as a point-of-care (POC) test for reasons of implementation. CRP and lactate measurement are part of the standard care in patients with suspected sepsis during assessment in the Emergency Department (ED) in the Netherlands. Procalcitonin (PCT) is not routinely measured in most hospitals, but we decided to include PCT as a candidate predictor as PCT might be superior to CRP [19], and the NICE sepsis guideline recommends research to further evaluate the use of PCT POCT for diagnosing serious bacterial infection and initiating antibiotic therapy. CRP, lactate, and PCT are currently available as POC tests.

### Outcome measures

The primary outcome measure is sepsis within 72 h after inclusion. This will be determined by an expert panel using the Sepsis-3 criteria [1]. The operational definition of sepsis is the presence of infection and a SOFA score (Table 2) of at least two above the baseline (which can be assumed to be zero in patients not known to have preexisting organ dysfunction).

**Table 2 Tab2:** SOFA score

System	Score			
	1	2	3	4
Respiration				
PaO_2_/FiO_2_, mmHg	< 400	< 300	< 200 with respiratory support	< 100 with respiratory support
Coagulation				
Platelets, × 10^3^/μl	< 150	< 100	< 50	< 20
Liver				
Bilirubin, μmol/l	20–32	33–101	102–204	> 204
Cardiovascular				
Hypotension	MAP < 70 mmHg	Dopamine ≤ 5 or dobutamine (any dose)^a^	Dopamine 5.1–15, or epinephrine ≤ 0.1, or norepinephrine ≤ 0.1	Dopamine > 15, or epinephrine > 0.1, or norepinephrine > 0.1
Central nervous system				
Glasgow Coma Score	13–14	10–12	6–9	< 6
Renal				
Creatinine, μmol/l	110–170	171–299	300–440	> 440
Urine output, ml/day			< 500	< 200

Adapted from Vincent et al. [20]

*PaO*_*2*_ partial pressure of arterial oxygen, *FiO*_*2*_ fraction of inspired oxygen, *MAP* mean arterial pressure

^a^Adrenergic agents administered for at least 1 h (doses given in μg/kg/min)

To limit the workload for the experts, we will appoint three expert panels, each comprising a GP, an emergency physician, and an internist(-intensivist). Each case will be assessed by one panel. All relevant information from medical records from the GP and the hospital when applicable will be presented to the panel (see Additional file 1). If there is no consensus on the primary outcome, the case will be discussed in a face-to-face consensus meeting with all three experts to determine the final outcome. Interobserver agreement between the three panels will be assessed in a selection of 10% of the cases that will be assessed by all panels. Besides the dichotomous primary outcome “sepsis within 72 h”, the likelihood of sepsis will be assigned a numerical score between 0 and 10. This gives information on the remaining uncertainty regarding sepsis classification, providing insight in the degree of bias that may be introduced when calculating diagnostic accuracy measures using dichotomous sepsis classification [21]. Furthermore, the need for hospital treatment is scored between 0 and 10 by the expert panel as a secondary outcome. An average score above 5 will be regarded as a patient that should best be referred to the hospital immediately by the GP and a score ≤ 5 as a patient that does not have to be referred immediately.

Other outcome measures are hospitalisation (length of stay and type of care: ICU or regular ward), maximum SOFA score in the first 72 h, 30-day all-cause mortality, final diagnosis, and medical costs.

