#### Procedure during home visit

All patients will receive usual care. Patients will be screened for eligibility during home visits by the attending GP of the GP cooperative. Verbal informed consent will be obtained from the patient or his legal representative. The GP will be (routinely) accompanied by a chauffeur during the home visit. The chauffeurs are used to practically assist the GP during the visit. Portable monitors (Philips intelliVue MP2 or X2) will be available to record peripheral oxygen saturation, automated blood pressure, and heart- and respiratory rate by three lead electrodes on the chest.

The GP will record the assessment of the candidate predictors in a case report form. In addition, the GP will record if he/she has a gut feeling that “something is wrong” and will provide the likelihood of the presence of sepsis at inclusion on a scale from 0 to 10.

All study materials will be taken to the patient’s home in a study bag. The venous samples will be collected by either the GP or an on-call laboratory assistant or nurse within 1 h after inclusion, with a maximum of 8 h. Written informed consent will be obtained prior to the collection of the blood samples. In case the patient is referred to the hospital and the blood samples are not collected by the GP, the study bag will be transported with the patient to the ED. Subsequently, the laboratory assistant on call will visit the patient in the hospital and collect the blood samples. Three blood tubes will be collected: 10 ml for serum, 10 ml for EDTA plasma, and a 2-ml heparin tube. Lactate will be measured immediately afterwards from a single drop of blood taken from the heparin tube, using the StatStrip Xpress (Nova Biomedical) POC test. The remaining blood samples will be taken to the hospital laboratory and divided into six samples of serum and six samples of EDTA plasma. The aliquots will be temporarily stored at the local laboratory at < − 70 °C. Two samples (1 ml serum and 1 ml EDTA plasma) will be transported to the Jeroen Bosch Hospital for CRP and PCT analyses, and the remaining samples (5 × 0.5 ml serum and 5 × 0.5 ml EDTA plasma) will be stored for 15 years at < − 80 °C at the UMC Utrecht for potential future testing.

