#### Data extraction

Relevant medical information will be obtained from the patient’s (regular) GP, the GP cooperative, and the hospital. Information from all hospital admissions in the 30-day follow-up will be retrieved, first by digital search in the local hospital and secondly by manual screening of the GP record for admissions in other hospitals. Medication use and comorbidities before inclusion will be retrieved from GP electronic records, as well as information on any subsequent contacts. The medical record of the assessment at the time of inclusion will be retrieved from the GP cooperative. The following data from the electronic medical record of the hospital will be collected: full reports from ED and hospital discharge; date and time of ED visit, hospital admittance, and discharge (including type of ward); vital signs, EMV score, leucocyte count, thrombocyte count, creatinine, bilirubin, CRP, and lactate measured in the first 72 h after inclusion; cultures taken in the first 72 h after inclusion; radiodiagnostic procedures in the first 7 days after inclusion; antibiotic prescriptions during hospitalisation; and intravenous volume therapy in the first 72 h (defined as more than 1.5 l of fluids in 24 h).

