### Sample size

In total, 12 candidate predictors are chosen for the development of the prediction model (Table 1). Using the rule of thumb of 10 events per variable [23], we need 120 patients reaching the primary outcome “sepsis within 72 h after inclusion” in the final dataset. Prior to the start, the prevalence of sepsis based on previous research and literature was estimated to be around 12%. However, preliminary data analysis from the patients included in the study so far indicates the prevalence of sepsis in the study cohort to be around 30–40%. After the first 100 cases will be assessed by the expert panel, we will determine the final target sample size.

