## Discussion

The TeSD-IT study is a diagnostic and prognostic study, designed for the development of a clinical prediction rule for the early recognition of sepsis in primary care. A limited number of nine clinical parameters and three blood tests were selected. This will enable us to construct the model using multivariable logistic regression techniques with 120 events included in the dataset. We realise the validity of rule of thumb of 10 event per variable is debated [27]. However, using an alternative sample size calculation suggested by van Smeden [28] results in a similar identical sample size of about 350 patients in case of 12 variables, an outcome rate of 0.35, and rMPSE set at 0.09. We have chosen to recruit patients in the setting of out-of-hours home visits performed by a GP. In this setting, GPs frequently encounter seriously ill patients in whom they instantly have to decide whether or not to refer the patient (immediately) to the hospital. A methodological advantage is that the required sample size is substantially lower than in other primary care settings with a lower incidence of sepsis. However, external validation in other settings and populations will be needed before implementing the clinical prediction rule more broadly.

The diagnosis of sepsis is not straightforward. In 2016, new consensus definitions for sepsis were published, which we try to implement as well as possible. As both the presence of infection as well as organ failure can be equivocal, we will use expert panels to determine the final outcome. The outcome should be clinically relevant for the GP. The rationale of the timeframe of 72 h is that patients who are found septic within this period after GP assessment would likely benefit from immediate hospital referral. Not all patients with organ failure need hospital treatment to recover, and not all patients with severe infections that are treated with intravenous antibiotic therapy have signs of organ failure. However, we believe the diagnosis of sepsis based on the Sepsis-3 definitions is the most relevant endpoint for GPs to differentiate between patients who are likely to benefit from immediate hospital treatment and patients who might be treated at home successfully. The expert panel will also rate the need for hospital treatment for every patient, regardless of the diagnosis. This will enable us to evaluate the effect of the new clinical prediction rule on medically unnecessary referrals.

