The expert panels will be instructed to use the SOFA score (increase, due to infection, of ≥ 2 points from baseline) to define the primary outcome “sepsis within 72 h after inclusion”. This is consistent with the Sepsis-3 consensus definition and leads to an objective and reproducible endpoint in the absence of a gold standard. However, this approach introduces the risk of incorporation bias. Parameters included in the SOFA score are more likely to be predictive of sepsis in our model. However, the blood tests (CRP, lactate, and procalcitonin) are not included in the SOFA score, which limits the risk of incorporation bias for these tests. Furthermore, vital signs measured in the first 72 h will be used to calculate the SOFA score and not only at the time of inclusion.

Patients will receive a questionnaire at day 30 measuring EQ5D-5L. The results may be biased due to selective response and poor recall due to sepsis- or age-related cognitive impairment. Imputation of the missing answers on the questionnaires will reduce this form of bias as much as possible. Furthermore, the development of the clinical prediction rule is not affected, as the patient questionnaires will only be used for the cost-effectiveness analyses

To compare the performance of the new clinical prediction rule with usual care, not only the decision to refer the patient to the ED, but also the assessment of the GP of the likelihood of sepsis on a scale from 0 to 10 and the presence of a “gut-feeling something is wrong” will be used. We will examine if the prediction rule will outperform those assessments of the GP in order to likely improve the usual care.

Only three candidate blood tests were selected for the development of the prediction rule. Various other biomarkers have promising diagnostic and/or prognostic properties in patients with suspected sepsis [29, 30]. At the start of this study, sufficient evidence of the additional diagnostic and/or prognostic value above lactate, CRP, and PCT was lacking. However, sufficient blood samples will be stored for retrospective testing of multiple additional biomarkers.

Although to our best knowledge no clinical prediction rules for sepsis in primary care were previously developed, several sepsis screening tools were published for the ambulance setting [31]. However, none of those have adequate inclusion criteria, data collection, and clinically relevant endpoints for use in the primary care setting.

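### As planned, the SOFA laboratory items are verified mainly in patients who reach hospital within 72 h, so the primary outcome label partly depends on a GP decision informed by the predictors

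*Protocol article*

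**What the plan says.** Under Outcome measures, sepsis within 72 h is decided by an expert panel: "The operational definition of sepsis is the presence of infection and a SOFA score (Table 2) of at least two above the baseline". The panel sees GP records for all patients and hospital records where they exist.

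Under Data extraction, a list introduced by "The following data from the electronic medical record of the hospital will be collected" holds the platelet count, creatinine and bilirubin for the first 72 h. The 72-h vital signs and the EMV score are in the same list.

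Under Procedure during home visit, all patients receive usual care. Blood is taken once, within 8 h at most. Lactate is measured at once, and 1 ml of serum and 1 ml of EDTA plasma "will be transported to the Jeroen Bosch Hospital for CRP and PCT analyses". The remaining serum and plasma are stored. No SOFA item is measured on study blood.

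The Discussion names incorporation bias, notes that CRP, lactate and PCT lie outside SOFA, and adds that "vital signs measured in the first 72 h will be used to calculate the SOFA score and not only at the time of inclusion". It describes the endpoint as objective and reproducible. It does not mention that verification depends on reaching hospital.

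**The concern.** The GP who records mental status, blood pressure, saturation and the other predictors also decides on referral. Referral largely decides whether the laboratory part of SOFA is ever measured. The same outcome label can therefore rest on different evidence in referred and home-treated patients, and the difference is linked to the predictors.

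Two results are at stake. One is the apparent performance of the clinical model; bootstrapping corrects optimism from model fitting but cannot correct a biased label. The other is the added-value analysis under Performance of the prediction model, where the GP's referral decision is itself a comparator.

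The reassurance about 72-h vital signs helps mainly those who reach hospital, because that is the record from which the repeated values are listed for extraction.

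**Working it through.** **1. The plan's own figures.** "In total, 12 candidate predictors are chosen for the development of the prediction model" and "Using the rule of thumb of 10 events per variable [23], we need 120 patients reaching the primary outcome": 12 × 10 = 120 events. With "an outcome rate of 0.35, and rMPSE set at 0.09", the event rule gives 120 / 0.35 = 343, against a calculation that "results in a similar identical sample size of about 350 patients in case of 12 variables"; 350 × 0.35 = 122.5 events. These figures reproduce, and this point changes none of them. It concerns what the label means.

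**2. What Table 2 allows in each setting (baseline zero).**
- Reached hospital: creatinine of 171 μmol/l or more, bilirubin of 33 μmol/l or more, or platelets below 100 each give 2 points alone.
- Stayed home without laboratory results: the cardiovascular item gives at most 1 point without vasoactive drugs (MAP below 70), and respiration needs PaO2/FiO2. Two points then come essentially from a Glasgow score of 12 or less, from 13–14 plus MAP below 70, or from the panel's view of oxygenation. These overlap with mental status, systolic pressure and saturation in Table 1.

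**3. Direction and size.** The article gives neither the share referred nor the share of septic patients missed without laboratory tests, so both are assumed. Simulation of 1,000,000 patients:
- clinical score X ~ N(0,1); true sepsis Y with logit P = a + X, prevalence set to 0.35; true AUROC 0.741;
- referral R with logit P = r + gX, set to 40%, 60% or 80%;
- a share m (25%, 50%, 75%) of septic, non-referred patients labelled non-septic; no false-positive labels.

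| Dependence of referral on the score | Change in AUROC |
|---|---|
| None | −0.048 to −0.006 |
| OR 2.7 per SD | +0.005 to +0.034 |
| OR 7.4 per SD | +0.010 to +0.073 |
| OR 1.65 per SD, GP also detects sepsis beyond the score, 60% referred | +0.001 to +0.005 |

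In the OR 2.7 and 7.4 rows the observed prevalence falls from 0.35 to between 0.22 and 0.34.

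**4. Hand checks.**
- With no dependence, missed cases are a random sample of cases mixed into the controls. At 40% referral and m = 0.75 the missed fraction is 0.60 × 0.75 × 0.35 = 0.1575. Observed AUROC = (0.65 × 0.741 + 0.1575 × 0.5) / (0.65 + 0.1575) = 0.694, as simulated.
- If s is the true sensitivity of GP referral, its observed value is s / [s + (1 − s)(1 − m)]. At 60% referral and OR 2.7, s = 0.71; with m = 0.5 this is 0.71 / (0.71 + 0.145) = 0.83, as simulated. The expression exceeds s whenever m > 0 and s < 1, so this bias has one direction.

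**The case against.** Much can be said for the plan, and most of it limits the point without removing it.

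- A reader might infer that only patients sent in by the visiting GP can be verified. The article does not support that. Data extraction covers all admissions during follow-up, including other hospitals, so a patient who deteriorates at home and reaches hospital within 72 h is verified. This lowers m.
- A reader might infer that home-treated patients are labelled non-septic because nothing was measured. No section scores unmeasured follow-up items as zero; the zero assumption is for the baseline. Three specialties judge each case, GP records may hold some test results, and the file describing the panel's information is not shown. The share m is therefore an assumption.
- The panel's 0–10 likelihood of sepsis is already meant to show how far a dichotomous label may mislead. It is a real partial safeguard, although it comes from the same panel judging the same incomplete information.
- A reader might infer that the model will certainly look better, by the top of the range. That needs referral to follow the predictors strongly, which no figure in the article shows.
- A reader might also infer a known tilt in the comparison with SIRS, NEWS and qSOFA, or in the added value of the blood tests. The existing scores share many of the same signs and would probably shift too; the check used one clinical score and cannot settle either question.

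What stands is the asymmetry itself: no SOFA laboratory item is planned outside the hospital record, and the Discussion's account of bias leaves this out.

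**Conclusion.** The point holds as differential verification that depends on reaching hospital, added to the acknowledged incorporation bias. It rests on what the article states about sources of SOFA data and uses of study blood, not on details left to a fuller document.

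Inflation of the clinical model's AUROC is the probable direction, since GPs are likely to refer on the signs they have just assessed. Its size is unknown: about +0.005 to +0.07 with clear dependence, near zero with weak dependence, negative with none. These figures assume a true prevalence of 0.35, 40–80% referred and 25–75% of non-referred sepsis missed. If any such sepsis is missed, the GP's referral decision gains apparent sensitivity whatever the dependence. The comparison of the model with usual care may therefore be distorted, possibly against the model.

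This calls for a low-cost improvement and a more careful claim. It does not show that the study cannot answer its question.

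**What to change.** - Measure creatinine and bilirubin in serum already collected from every participant: the shipped 1 ml aliquot if its volume suffices, otherwise a stored 0.5 ml aliquot. The laboratory should confirm that volume and frozen storage suit both assays, as the article does not say. Give the results to the panel for all patients, referred or not.
- Report how many primary outcomes were laboratory-verified, by referral status.
- Pre-specify a sensitivity analysis of the primary outcome using the existing 0–10 likelihood score.
- Qualify the Discussion's claim of objectivity and reproducibility, and name referral-dependent verification beside incorporation bias.

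The cost is two routine assays for about 350 patients, one addition to the panel's file, one table and one analysis, with no new sampling. The correction is partial: the sample is one early value (within 8 h), not a 72-h maximum, and platelets and PaO2/FiO2 stay unmeasured at home. The Sample size section still describes assessment of the first 100 cases by the panel as to come, so on the article's own account the change is timely.
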